### Interim analyses {21b}

There are no plans to perform an interim analysis or stopping guidelines.

### Methods for additional analyses (e.g. subgroup analyses) {20b}

As yet, there is no plan to perform subgroup or post-hoc statistical analysis.

### Methods in analysis to handle protocol non-adherence and any statistical methods to handle missing data {20c}

The primary analysis will be conducted on the modified Intention-to-Treat population, with outcome data for all participants analysed according to their random group allocation, regardless of the actual intervention received (i.e., Bier block or UGSCB) or the occurrence of protocol deviations. Notably, only participants with complete primary outcome data will be included. As Intention-to-Treat analysis may bias towards a finding of no effect, Per-Protocol analysis will also be performed and reported alongside the primary analysis. The Per-Protocol population will consist of all participants who received their allocated intervention and who had no protocol deviation expected to affect the efficacy of regional anaesthesia and analgesia.

The primary outcome will be analysed using complete case data. Missing data will be reported but not imputed. If the proportion of missing data is non-negligible, multiple imputation of missing data will be performed.

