### Criteria for discontinuing or modifying allocated interventions {11b}

Should the participant demonstrate inadequate anaesthesia from either UGSCB or BB, as evidenced by the inability to tolerate closed reduction of the injured part, the treating clinician can choose an additional or alternative method that will allow the participant to undergo safe and comfortable closed reduction of the injured limb. The choice of technique will be at the discretion of the treating clinician in consultation with the patient, and may include the use of inhaled nitrous, performing the alternative trial intervention (BB or UGSCB), IV procedural sedation, or abandonment and referral to a centre with theatre access for orthopaedic procedures.

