### Sample size {14}

Sample size calculations were based upon a hypothesis of non-inferiority of UGSCB compared to BB for the primary outcome measure of maximal pain during closed reduction. Sample size calculations were based upon approximation to the normal distribution [14] using previous pain VAS scores reported by Kukreja et al. [9] and Beck et al. [15]. A non-inferiority margin of 20 mm was selected for power calculation. This was based on a previous study [15] that compared Bier block to a periosteal block (i.e., injection of local anaesthetic at the fracture site) for closed reduction of distal radius fractures. That study showed median pain VAS during closed reduction was 5 mm for Bier block and 26 mm for periosteal block (i.e., difference of 21 mm on pain VAS, which was rounded to 20 mm), but both techniques provided adequate anesthesia for tolerance of closed reduction procedure. Thus, a non-inferiority margin of 20 mm difference in mean VAS score was selected for the trial.

Assuming a non-inferiority margin of 20 mm difference in the mean VAS pain score, expected standard deviation of 30 mm [9], alpha 0.025 and a power of 80%, we would require primary outcome data for 72 participants. Allowing for an attrition rate of 5%, we estimate that we would require a total sample size of 76 participants for the study (i.e. 38 participants per group).

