## Statistical methods

### Statistical methods for primary and secondary outcomes {20a}

Group data will be used for data and statistical analysis. Data will be summarised as mean (standard deviation) or median (interquartile range) for continuous variables, depending on the normality of their distribution, and as frequency (percentage) for categorical variables. The primary outcome of pain intensity during the procedure will be assessed as a non-inferiority hypothesis using data from the 10 cm VAS tool. The between-group difference in pain intensity will be assessed using linear regression modelling with group allocation (UGSCB vs BB) included as a main effect. A conclusion of non-inferiority will be determined if the 95% confidence interval for the between-group difference in mean maximal pain is entirely below the non-inferiority margin. Analysis will be performed on an intention-to-treat basis, with a per-protocol analysis of the primary outcome also included as a key secondary finding.

For analysis of other secondary outcomes, linear regression modelling will be used to compare continuous outcome data, including between-group difference in patient satisfaction on the 10 cm VAS satisfaction scale and total opiate dose in mg of morphine equivalent. Difference in median procedural time and ED length of stay will be compared using median regression. Odds of dichotomous outcomes will be compared using logistic regression modelling. Formal adjustment for multiplicity will not be performed. Analysis will be performed on Stata (StataCorp, Texas USA), v14.2 or later.

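### The protocol has no pain-scoring rule for an abandoned reduction, so the complete-case primary analysis may lose participants for a reason tied to the outcome

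*Protocol article*

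**What the plan says.** Outcomes {12} defines the primary outcome as the worst pain felt during the reduction, marked by the participant on a 10 cm VAS straight after the reduction has been completed. It gives no other time of scoring.

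Criteria for discontinuing or modifying allocated interventions {11b} covers participants who cannot tolerate the reduction. The clinician may add nitrous oxide, use the other trial block or sedate, or may choose "abandonment and referral to a centre with theatre access for orthopaedic procedures".

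Section {20a} says "Analysis will be performed on an intention-to-treat basis". Section {20c} calls the primary population modified intention-to-treat, analyses people as randomised, and adds "Notably, only participants with complete primary outcome data will be included". Per-protocol analysis of the same outcome is reported alongside.

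On missing scores, {20c} says "Missing data will be reported but not imputed" and then "If the proportion of missing data is non-negligible, multiple imputation of missing data will be performed". It does not say which result would decide non-inferiority if imputation were triggered.

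**The concern.** Each rule is ordinary by itself; the difficulty lies in the combination. Abandonment follows from being unable to tolerate the reduction, which is close to the quantity the primary outcome measures. If the only stated scoring moment is completion, an abandoned case may have no score, and the complete-case rule then removes it. The missingness would be related to the outcome.

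The per-protocol analysis, added because intention-to-treat may favour a finding of no effect, uses the same score and cannot bring these participants back. Imputation that assumes data missing at random would not repair this unless its model carried information on block failure, because it would otherwise draw values from people who tolerated the reduction.

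Abandonment is foreseeable. Study setting {9} describes limited weekday orthopaedic cover and none after hours, and Outcomes {12} counts transfers and later procedures at another hospital. What is at stake is whether a handful of the worst failures could leave the comparison against a 20 mm margin.

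**Working it through.** **1. The plan's own figure.** Sample size {14} gives "A non-inferiority margin of 20 mm was selected for power calculation", and "expected standard deviation of 30 mm [9], alpha 0.025 and a power of 80" per cent. Taking alpha as one-sided and the true difference as 0 (not stated, but it reproduces the result):

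n per arm = 2 × (1.96 + 0.8416)² × 30² / 20² = 35.3, so 36, or 72 in all. This agrees with "we would require primary outcome data for 72 participants". Then 72 / 0.95 = 75.8, so 76, or 38 per arm. The plan's size is correct. The attrition allowance is 76 − 72 = 4 participants over both arms.

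**2. What is assumed.** The documents give neither the number of abandoned reductions nor their pain scores. I assume k of 38 abandoned in the supraclavicular arm and none in the Bier block arm; a score S of 90 to 100 mm for the abandoned cases; a Bier block mean m of 20 to 30 mm; SD 30 mm among scored participants.

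**3. How much difference is hidden.** If the scored participants do not differ between arms, the difference over all randomised is k × (S − m) / 38, while the complete-case comparison expects 0.

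- k = 2: from 2 × 60 / 38 = 3.2 mm to 2 × 80 / 38 = 4.2 mm.
- k = 4: from 4 × 60 / 38 = 6.3 mm to 4 × 80 / 38 = 8.4 mm.

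**4. False non-inferiority.** Let the true difference over all randomised be exactly 20 mm. Among scored participants it is then d = (20 × 38 − k(S − m)) / (38 − k), with SE = 30 × √(1/38 + 1/(38 − k)). The chance that the upper 95% limit falls below 20 mm is about Φ((20 − d)/SE − 1.96). The last column is a simulation of the pooled t interval with 40,000 runs per case and normal scores not truncated at the ends of the scale.

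| k | S | m | d (mm) | SE (mm) | Formula | Simulated |
|---|---|---|---|---|---|---|
| 2 | 90 | 30 | 640/36 = 17.8 | 6.98 | 5.0% | 5.3% |
| 2 | 100 | 20 | 600/36 = 16.7 | 6.98 | 6.9% | 6.9% |
| 4 | 90 | 30 | 520/34 = 15.3 | 7.08 | 9.8% | 9.6% |
| 4 | 100 | 20 | 440/34 = 12.9 | 7.08 | 16.8% | 16.5% |

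The nominal rate is 2.5%.

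**5. When abandonment occurs in both arms.** Take all-randomised means of 25 mm (Bier block) and 45 mm (supraclavicular), abandoned cases at 100 mm, and SE = 30 × √(2/36) = 7.07.

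- Two per arm: (1710 − 200)/36 − (950 − 200)/36 = 41.9 − 20.8 = 21.1 mm. Φ((20 − 21.1)/7.07 − 1.96) = 1.7%, below nominal.
- Three against one: (1710 − 300)/35 − (950 − 100)/37 = 40.3 − 23.0 = 17.3 mm, giving 5.7%.

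**6. Milder scores.** With the same means and abandoned supraclavicular cases at 70 mm, none in Bier block: two lost gives 3.9% and four gives 6.1%.

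**The case against.** The strongest reply is that the protocol nowhere says an abandoned case goes unscored. The outcome is maximal pain during the reduction; a failed attempt has a maximum too, and staff could ask for it when the attempt stops. This stands: the missing score is an inference from the stated time of measurement, and what can be shown is that no rule covers an uncompleted reduction.

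A reader might infer that block failures in general are removed. The documents do not support that. Abandonment is one of several options in {11b}, people rescued by nitrous oxide, sedation or the other block can complete and be scored, and {20c} keeps them in their randomised arm. Treatment failure, sedations and transfers are also compared as secondary outcomes.

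A reader might infer that the bias must favour the supraclavicular block. It does so only if abandonment is commoner in that arm. The short training route in {11a}, a one-hour workshop and at least two supervised blocks, makes this plausible, but the background lists practical limits of Bier block too, and step 5 shows the effect vanishing or reversing when rates are equal.

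A reader might also infer that {20a} and {20c} contradict each other on the population, and that the two imputation sentences do so as well. The first pair reads as shorthand followed by a definition, the second as a default with an exception. The cut-off and the imputation model may properly sit in an analysis plan that is not shown. What is left is that the decisive result is not named in advance.

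Finally, the 10–17% range puts the whole two-arm allowance of four into one arm (4/38 = 10.5%), and {18b} expects little attrition. That is fair, so the range is an illustration and not a forecast.

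**Conclusion.** The point holds in a limited form. Followed as written, the plan can drop a participant from both the primary and the per-protocol analysis because the reduction could not be tolerated, and it gives no rule to prevent this. How often that would happen, and in which arm, cannot be known from the documents.

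Under the one-sided assumptions in the working, two lost of 38 move the false non-inferiority rate from 2.5% to about 5–7%, and four move it to about 10–17%. Balanced abandonment largely removes the effect, and lower pain scores shrink it. These figures do not show that the trial will be biased. They show that very few participants could matter, which is reason enough to close the gap in advance. The sample size of 76 is not in question.

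**What to change.** 1. In Outcomes {12}, state that maximal pain is scored when the reduction is completed or when the attempt stops, whichever comes first.
2. In {20c}, keep every randomised participant with such a score in the primary analysis, and state in advance that the complete-case result is primary and multiple imputation supportive.
3. Add a sensitivity analysis, applied to both arms, that gives participants with no score because of block failure a prespecified unfavourable value (for example 100 mm), or a tipping-point analysis by arm. Require the non-inferiority conclusion to be discussed against it.
4. Use one population name in {20a} and {20c}.

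I would not make 100 mm the primary score. It turns reported pain into a composite and costs power: with four of 38 supraclavicular participants kept at 90–100 mm and the others not differing, the simulated chance of declaring non-inferiority is 27–44%, against 79–80% in complete cases. It fits better as a sensitivity analysis.

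The cost is one extra scoring instruction, some extra analysis, and a less favourable estimate with a wider interval if failures occur.

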### Plans to give access to the full protocol, participant level-data and statistical code {31c}

Data associated with published work will be available upon reasonable request. Should this occur, only de-identified data will be made available to protect participant confidentiality.

## Oversight and monitoring

### Composition of the coordinating centre and trial steering committee {5d}

The coordinating centre is the ED at Redland Hospital in Brisbane, Australia. The trial steering committee consists of the principal investigator (HT) and co-investigations (CT, MT, PJ and PS), who are responsible for participant recruitment, execution of the research protocol, data collection and entry. All members of the trial steering committee are Good Clinical Practice certified.

### Composition of the data monitoring committee, its role and reporting structure {21a}

The Research Governance Office (RGO) of Metro South Hospital and Health Service will ensure the safety of the trial participants by monitoring the ethical conduct of the research study, ensuring that the trial is conducted according to the protocol and that data are collected appropriately.

### Adverse event reporting and harms {22}

Potential harm from UGSCB and BB are listed in Table 3.

**Table 3 Tab3:** Potential harm/adverse effects

UGSCB	BB
Pain during injection and bruising	Pain during insertion intravenous catheter
Infection	Discomfort of cuff inflation
Injury to major blood vessels or nerves	Infection
Puncture of the lungs	Local bruising
Respiratory distress from phrenic nerve paralysis	Methaemoglobinaemia
Local anaesthetic toxicity	Local anaesthetic toxicity

*UGSCB* Ultrasound-guided supraclavicular block, *BB* Bier block

The occurrence of potential adverse events will be systematically checked from a list and prospectively recorded on the clinical research form. Additionally, other adverse events will be captured from the open-ended question “Were there any other adverse events not listed?” All harms encountered in the trial will be reported in the final report. The principal investigator will report any serious events to the institutional HREC within 72 h of the notice.

### Frequency and plans for auditing trial conduct {23}

Annual progress reports will be submitted to the RGO and the institutional Human Research Ethics Committee (HREC) each year the project is active, and a final report will be submitted on completion of the study. This will include details on trial status, adverse events, complaints and any protocol deviations.

### Plans for communicating important protocol amendments to relevant parties (e.g. trial participants, ethical committees) {25}

Amendments to the research protocol including those that may affect the ongoing ethical acceptability of a protocol will be submitted to the institutional HREC for approval prior to implementation. If approved, changes to the protocol will be communicated through email to the research investigators and treating clinicians involved.

### Dissemination plans {31a}

The findings of the SUPERB study will be disseminated through peer-reviewed publication(s) and academic conference presentations.

## Discussion

The SUPERB trial is novel and could have significant findings that benefit patients and the health care system. This will be the first randomised controlled trial to elucidate the effectiveness and safety of UGSCB compared to BB for the closed reduction of upper limb injuries in the ED. Previous evidence for the efficacy of UGSCB predominantly arise from trials performed by trained anaesthetists in an operating theatre setting [9, 10]. Existing evidence from an ED perspective arise from two case series [7, 16] and a small prospective study [8]. Notably, Stone et al. [8] published a small prospective study including 12 subjects that showed UGSCB was effective and less time consuming when compared to procedural sedation for management of upper limb injuries. Findings from the SUPERB trial could shape future choice of management of upper extremity emergencies.

Further, we anticipate that this research will foster interest in future studies to examine other regional block procedures in the ED, which is rapidly becoming an emerging niche. From the patient perspective, UGSCB may provide additional benefits such as medium-term analgesia, reduction of opioid requirements, and the potential to enhance patient satisfaction. From a departmental/systems perspective, there is potential for UGSCB to reduce overall emergency length of stay, which may facilitate ED patient flow.

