**Discussion:**

Existing evidence suggests UGSCB is effective when performed in the operating theatre by trained anaesthetists. SUPERB will be the first randomised controlled trial to elucidate the effectiveness and safety of UGSCB in the ED. The findings have the potential to provide an alternative safe and effective option for the management of upper extremity emergencies in the ED.

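### The protocol offers safety as a possible conclusion, but 38 patients per arm and a logistic odds comparison of harms cannot support one

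*Protocol article*

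**What the plan says.** Safety appears in four places. The Abstract (Background) and Background and rationale {6a} both treat it as unknown whether UGSCB is safe in the ED. The Abstract (Discussion) says: "The findings have the potential to provide an alternative safe and effective option for the management of upper extremity emergencies in the ED". The main Discussion says: "This will be the first randomised controlled trial to elucidate the effectiveness and safety of UGSCB compared to BB".

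The formal hypothesis is narrower. Objectives {7} attaches non-inferiority to procedural pain and lists adverse events among the secondary objectives, with comparison to Bier block (BB). Sample size {14} rests on pain alone: "a non-inferiority margin of 20 mm difference in mean VAS score was selected for the trial", and "we estimate that we would require a total sample size of 76 participants for the study (i.e. 38 participants per group").

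Statistical methods {20a} gives a confidence-interval rule for pain. For dichotomous outcomes it says: "Odds of dichotomous outcomes will be compared using logistic regression modelling". It does not name adverse events there, but no other inferential method in the document fits them. No margin, precision target or excludable rate is given for any harm.

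Harms are also handled descriptively. Adverse event reporting and harms {22} provides a checklist, an open question and full reporting. Provisions for post-trial care {30} compares type and severity between groups. Outcomes {12} adds an email contact 24 to 72 hours after discharge.

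**The concern.** Pain has a margin and a bound that must be met. Safety has neither, although it is part of the stated question and of the hoped-for result. An odds comparison looks for a difference. It does not say how large a harm the data can exclude, and that is what a statement about safety needs.

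The harms at issue are probably uncommon. Table 3 lists lung puncture, respiratory distress from phrenic nerve paralysis and major vessel or nerve injury for UGSCB but not for BB, and methaemoglobinaemia for BB only. For such events one arm may well have none, and the logistic odds ratio then breaks down. At stake is how far the report can go beyond pain when it recommends UGSCB as an alternative.

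**Working it through.** **Inputs from Sample size {14}:** margin 20 mm, SD 30 mm, alpha 0.025 (taken as one-sided), power 80%, 72 evaluable, 5% attrition, 76 in total, 38 per arm. The document gives no harm rates, so every harm rate below is an assumption.

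**1. The plan's own figure.** n per arm = 2 × (1.960 + 0.842)² × 30² / 20² = 35.3, rounded up to 36, so 72 in total. Then 72 / 0.95 = 75.8, rounded up to 76. The figure reproduces, and it uses pain inputs only.

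**2. What zero events would exclude.** The exact upper limit for 0 of n is 1 − a^(1/n).
- Two-sided 95%: 1 − 0.025^(1/38) = 0.0925, or about 9.3%.
- One-sided 95%: 1 − 0.05^(1/38) = 0.0758, or 7.6%.

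**3. Chance of never seeing a real complication in the UGSCB arm**, (1 − p)^38:
- 1% true rate: 0.99^38 = 0.68
- 2%: 0.98^38 = 0.46
- 5%: 0.95^38 = 0.14

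**4. What equal counts leave open.** The Newcombe 95% upper limit for the UGSCB minus BB risk difference at 38 per arm is +9.2 percentage points for 0 v 0, +11.1 for 1 v 1, +12.6 for 2 v 2 and +15.0 for 4 v 4.

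**5. Power of a difference test at 38 per arm**, two-sided 0.05, by full enumeration of two binomials. Fisher's test is a reference only, because the protocol does not name it. The likelihood-ratio test is one that a logistic model can supply.

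| Assumed BB v UGSCB rate | Fisher | Logistic likelihood ratio |
|---|---|---|
| 2% v 10% | 9% | 41% |
| 5% v 15% | 16% | 35% |
| 5% v 20% | 38% | 56% |
| 10% v 30% | 50% | 61% |
| 2% v 20% | 60% | 82% |
| 5% v 30% | 79% | 87% |

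The likelihood-ratio gain comes partly from a liberal test: with both true rates at 5% it rejects in 9.1% of trials instead of 5%.

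**6. Zero cells.** With no events in one arm the maximum-likelihood odds ratio is zero or infinite. With none in either arm it is undefined. The test result then depends on the method: 3 v 0 events gives p = 0.039 by likelihood ratio and 0.24 by Fisher, and 5 v 0 gives 0.007 and 0.054. The protocol does not say which test the logistic comparison would use.

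**The case against.** A reader might infer that a non-significant harm comparison will be reported as proof of safety. The document does not say so. No rule for concluding safety appears anywhere, and the only non-inferiority decision concerns pain. This objection stands in full.

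Nor is the odds comparison the only treatment of harms. They are itemised, compared by type and severity, and all reported. Logistic regression normally yields a confidence interval, at least when both arms have events. These points also stand, although listing events sets no limit on the rate that the data exclude.

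A reader might further infer that the comparison would miss most excess harm that matters. That depends on assumed rates and on the test. On the likelihood-ratio test, 5% v 20% and 10% v 30% are detected more often than missed, and the document defines no relevant excess.

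It can also be said that sizing a trial on its primary outcome is ordinary practice, that the safety wording is cautious prose in the Abstract and Discussion, and that finer harms analysis belongs in an analysis plan that is not shown. The first is fair, and the sample size is not faulted here. On the others, the odds-comparison method and the safety wording are both printed in this document. A later plan could add intervals, but it would not make 76 patients support the word safe.

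**Conclusion.** The point holds as an unsupported safety claim joined to a poorly suited harms analysis. It is not a stated wrong decision rule, and the primary pain analysis is unaffected.

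The firmest figures need no assumed rate difference: 0 of 38 leaves rates up to about 9.3% open, and zero events in an arm gives no finite odds ratio. A 1% complication, if that were the true rate, would be missed altogether in 68% of trials. The power figures (16% to 35% for 5% v 15%) are illustrations. All figures take 38 analysed per arm; with fewer patients the limits widen.

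**What to change.** In Statistical methods {20a}, replace the logistic odds ratio for harms. For each Table 3 complication, and for any serious block complication, report the rate in each arm with an exact 95% confidence interval, and the UGSCB minus BB risk difference with its 95% interval. Add that a non-significant difference is not evidence of safety, and state in advance that 0 of 38 excludes only rates above about 9%.

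In the Abstract (Discussion) and the main Discussion, limit the claim to non-inferior procedural pain, with harms described and the upper limit that the data can exclude.

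This needs wording changes and a few intervals, with no extra patients or data. The cost is a more modest safety claim.
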